
### Sample size

This study aims to investigate whether EA at specific acupoints can reduce the incidence of POD among elderly patients undergoing LRP. The sample size was calculated based on previous reports and our preliminary pilot study. According to earlier research, the incidence of POD in patients undergoing LRP is approximately 21%. In our preliminary pilot study involving 40 elderly patients undergoing LRP (*n* = 20 per group), the incidence of POD was 25% in the sham SEA group and 10% in the EA group. Furthermore, recent evidence in high-risk elderly populations has shown that electroacupuncture can significantly reduce the incidence of postoperative neurocognitive disorders, with reductions comparable to those observed in our pilot data (34). Considering these findings, it is hypothesized that the incidence of POD after treatment will decrease from a baseline of 20% to 8%. With a significance level set at 0.05 and a statistical power of 0.8, the required sample size to detect a significant difference between the two groups is 101 patients per group. Allowing for a potential 5% loss to follow-up, a total of 212 patients will be enrolled in this study.

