### Randomization and blinding

Randomization will be performed by an independent statistician using SPSS software version 26.0, generating a random number sequence to assign participants in a 1:1 ratio to either the EA or SEA group. To ensure a balanced distribution between the two study sites, randomization will be stratified by center utilizing a block randomization method with varying block sizes of 4 or 6. The allocation sequence will be concealed in sequentially numbered, opaque, sealed envelopes, which will be kept in a secure location and opened by the acupuncturist only after the participant has provided informed consent and completed baseline assessments. Given the nature of the intervention, the acupuncturist cannot be blinded to group allocation; however, to minimize bias, this study employs a patient- and assessor-blinded design. Participants will remain blinded to their treatment assignment through the use of a sham procedure with identical device settings (lights and sound), while outcome assessors—including anesthesiologists responsible for intraoperative management and research registrars conducting postoperative delirium assessments—will be strictly blinded to group allocation. Additionally, the statistician performing the final analysis will handle data with coded identifiers to maintain blinding until the analysis is complete, with emergency unblinding permissible only if essential for clinical management of a severe adverse event.

To evaluate the integrity of the blinding procedures, a standardized blinding assessment questionnaire will be administered to all participants immediately following the completion of the intervention. Participants will be required to quantify the intensity of the stimulation sensation—encompassing specific De qi characteristics such as soreness, numbness, distension, or heaviness—and report their perception regarding the nature of the treatment received. The specific details this assessment are presented in Table 2.

**Table 2 tab2:** Questionnaire for the assessment of blinding effectiveness and acupuncture sensation.

Blind Method Assessment Questionnaire
Name:________ Random Number:_________ Date:___________ **Please answer the following questions according to the latest acupuncture experience.**

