### Statistical analysis

All analyses will be conducted according to the ITT principle, in which all randomized participants will be analyzed in the group to which they were originally assigned, regardless of protocol adherence or the treatment ultimately received. Baseline demographic and clinical characteristics will be summarized to assess the balance achieved between the two groups by randomization. Continuous variables will be presented as means with standard deviations (SDs) or medians with interquartile ranges (IQRs) based on the normality of distribution, while categorical variables will be presented as frequencies and percentages. Between-group comparisons for baseline data will be performed using the independent samples *t*-test, the Mann–Whitney U test, or the *χ*^2^ test (or Fisher’s exact test, as appropriate).

The primary outcome is a binary endpoint, defined as the incidence of POD within the first three postoperative days. The primary hypothesis will be tested using a generalized linear mixed model (GLMM) with a binary logistic link function to estimate the adjusted odds ratio (aOR) and 95% confidence interval (CI) for the EA group compared with the SEA group. The model will be adjusted for three pre-specified baseline covariates: age, ASA physical status, and baseline MMSE score. To account for the clustering effect inherent in the multicenter design, the study center will be included in the model as a random effect. To quantify the clinical effect size, a supplementary analysis will be conducted. We will use a modified Poisson regression model with a robust error variance to directly estimate the adjusted relative risk (aRR) after adjusting for the same covariates. The absolute risk reduction (ARR) and the number needed to treat (NNT), with their corresponding 95% CIs, will then be calculated from the aRR. Missing data on the primary outcome will be handled using multiple imputation by chained equations (MICE) under the missing-at-random assumption.

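### The stated 101 patients per group gives 80% power only with a one-sided 5% test; under the two-sided analysis implied by the planned 95% CI, power is about 70%

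*Protocol article*

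**What the plan says.** The Sample size section hypothesises a drop in delirium incidence from 20% under sham to 8% under electroacupuncture. "With a significance level set at 0.05 and a statistical power of 0.8", it concludes that "the required sample size to detect a significant difference between the two groups is 101 patients per group", and it enrols 212 in total to allow for 5% loss. It gives neither the sidedness of the test nor the formula. As background, the same section reports a pilot with 20 patients per group, in which "the incidence of POD was 25% in the sham SEA group and 10% in the EA group".

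The Statistical analysis section tests the primary hypothesis with a logistic mixed model "to estimate the adjusted odds ratio (aOR) and 95% confidence interval (CI) for the EA group compared with the SEA group", adjusted for age, ASA status and baseline MMSE, with centre as a random effect. The article nowhere mentions a one-sided test, a directional significance level or a 90% interval.

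The limitations paragraph of the Discussion calls the assumed effect optimistic and says the trial may be underpowered if the true effect is smaller than projected.

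**The concern.** All the inputs and the result stand together in the Sample size section, so the figure can be recomputed, and 101 is well below what a two-sided 5% test requires for 20% versus 8%. A 95% confidence interval that excludes an odds ratio of 1 is conventionally a two-sided 5% test, which is stricter than a one-sided 5% test. If the sample size rests on the one-sided criterion and the analysis uses the two-sided one, the trial has less power than it claims, even when electroacupuncture works exactly as hypothesised.

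This affects how a non-significant result is read. A reader told that power was 80% at 20% versus 8% would count such a result more heavily against that effect than the design allows. The existing limitation does not cover this, because it ties low power to a smaller true effect.

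**Working it through.** **Inputs.** From Sample size: p1 = 0.20, p2 = 0.08, difference 0.12, significance level 0.05, power 0.80 (z = 0.8416). From Randomization and blinding: 1:1 allocation. Mean proportion 0.14. Variance sum 0.20×0.80 + 0.08×0.92 = 0.16 + 0.0736 = 0.2336. Sidedness is not given, so both readings are computed: z = 1.6449 (one-sided) and z = 1.9600 (two-sided).

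**Reproducing 101.** With unpooled variance, n = (z + 0.8416)² × 0.2336 / 0.12².

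- One-sided: (1.6449 + 0.8416)² × 0.2336 / 0.0144 = 100.3, rounded up to **101**, the protocol's figure.
- Two-sided: (1.9600 + 0.8416)² × 0.2336 / 0.0144 = 127.3, rounded up to **128**.

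With pooled variance, n = [z × √(2×0.14×0.86) + 0.8416 × √0.2336]² / 0.12².

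- One-sided: (0.8072 + 0.4068)² / 0.0144 = 102.3, rounded up to 103.
- Two-sided: (0.9618 + 0.4068)² / 0.0144 = 130.1, rounded up to **131**.

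**Other formulas**, to see whether any two-sided method gives 101:

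| Method | One-sided 5% | Two-sided 5% |
|---|---|---|
| Unpooled | 101 | 128 |
| Pooled | 103 | 131 |
| Arcsine | 99 | 126 |
| Pooled, continuity-corrected | 119 | 147 |
| Wald, log odds ratio | 110 | 140 |
| Wald, log relative risk | 115 | 145 |

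The smallest two-sided figure is 126. None is near 101.

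**Power at 101 per group, two-sided.**

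- Unpooled: standard error √(0.2336/101) = 0.04809; 0.12/0.04809 − 1.9600 = 0.535; power 70.4%.
- Pooled: null standard error √(2×0.14×0.86/101) = 0.04883; (0.12 − 1.9600×0.04883)/0.04809 = 0.505; power 69.3%.
- Exact enumeration of the uncorrected chi-square test: 71.0%.
- Wald test on the log odds ratio, unadjusted, the scale closest to the planned model: log OR = ln(0.25/0.08696) = 1.056; standard error √[(1/0.16 + 1/0.0736)/101] = 0.443; power about 66%.

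The one-sided unpooled power at 101 is 80.2%, which agrees with the stated 0.8.

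**Power if all 106 per group are evaluable, two-sided:** 71.4% (pooled), 72.4% (unpooled), 73.2% (exact chi-square), about 68% (log odds ratio).

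**Effect detectable with 80% two-sided power at 101 per group.** Solving the same formulas for p2 with p1 = 0.20 gives 6.7% (pooled) or 6.8% (unpooled), against the assumed 8%.

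**Size needed for 80% two-sided power at 20% versus 8%.** 128/0.95 = 134.7 and 131/0.95 = 137.9, so 135 to 138 per group, or 270 to 276 in total.

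**Allowance for loss.** 101 × 1.05 = 106.05, so 106 per group and 212 in total follow from 101 by the common multiplication. Dividing instead gives 202/0.95 = 212.6, a difference of less than one patient. This step is not at issue.

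**The case against.** The strongest reply is that the protocol declares neither sidedness. Its hypothesis is directional, and if a one-sided 5% test was intended, 101 is correct. The one-sided origin is indeed an inference from an exact match. But an undeclared one-sided 5% test does not correspond to the conventional 95% interval planned for the primary result, so the two sections would still have to be reconciled.

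The figure might instead come from the pilot rates. Tested two-sided, 25% versus 10% needs 99.5 (pooled) or 96.8 (unpooled) per group, close to 101 but not equal to it. The text ties 101 to 20% versus 8%, though, and two-sided power for those rates is about 70% wherever the number came from.

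The power figures above are for unadjusted comparisons, and adjustment for age, ASA status and MMSE could raise power somewhat. The documents give nothing from which to quantify this, and the sample size section claims no such gain. To rescue 101, adjustment would have to cut the required number by 21% (1 − 101/128) to 23% (1 − 101/131).

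Lastly, the limitations do warn about power and call the effect optimistic. That partly protects the reader, but the warning is conditional on a smaller effect and leaves the 80% claim standing at the assumed one.

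**Conclusion.** The concern holds. For 20% versus 8%, significance level 0.05 and power 0.8, a two-sided test needs 128 to 131 per group by the usual formulas; the stated 101 is what a one-sided 5% test needs. With 101 evaluable per group, two-sided power is 69–71%, so the risk of a non-significant primary result at exactly the assumed effect is about 30% rather than 20%. Full retention of 106 per group raises power only to 71–73%.

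This rests on two assumptions: that the planned 95% interval carries its conventional two-sided meaning, and that power is judged by an unadjusted comparison of two proportions. That the calculation was one-sided is the most likely explanation but is not documented; the shortfall does not depend on it.

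**What to change.** Keep 212 patients and correct the text.

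- **Sample size:** replace the present claim with wording such as: *With 101 evaluable patients per group and a two-sided 5% test, power to detect 20% versus 8% is about 70% (unadjusted comparison of two proportions); 80% power is reached for 20% versus about 6.7%.* The second figure describes what the design can detect and is not a new hypothesised effect.
- **Statistical analysis:** state that the primary test is two-sided at 5%, matching the 95% interval.
- **Limitations:** add that power is below 80% even if the assumed effect is exactly right.

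The cost is wording in three places and a less favourable stated power; no extra patients are needed. The sponsor could instead enlarge the trial to 270 to 276 patients to reach 80% two-sided power, or declare and justify a one-sided test with a matching interval. With enrolment open since March 2025 and expected to run to July 2026, restating the power is the least disruptive choice, and it should be made before the data are analysed.

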### Additional consent provisions for collection and use of participant data and biological specimens

Informed consent will be obtained from all participants prior to enrollment. The investigators will provide a detailed explanation of the study procedures, including the EA intervention across the preoperative, intraoperative, and postoperative phases. The Informed Consent Form (ICF) explicitly outlines the scope of data collection and the specific procedures involved. Regarding biological specimens, a 5 mL venous blood sample will be collected at two time points: immediately before anesthesia induction and at the end of surgery. The ICF includes a specific provision regarding the collection, analysis, and storage of these specimens. Participants will be given the option to consent to—or decline—the preservation of their biological samples for potential future ancillary studies. Refusal to consent to future sample storage will not affect their participation in the main trial.

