**Figure 1 fig1:**
[figure not shown]
Flow chart of the study procedure. The diagram outlines the study design and participant timeline, encompassing enrollment, screening for eligibility, baseline assessment, and randomization. A total of 212 eligible elderly patients undergoing laparoscopic radical prostatectomy (LRP) will be randomly allocated in a 1:1 ratio to either the electroacupuncture (EA) group (*n* = 106) or the sham electroacupuncture (SEA) group (*n* = 106). The chart details the intervention phase, postoperative follow-up, assessment of primary and secondary outcomes (including incidence of POD, biomarkers, and adverse events), and final data collection. POD: Postoperative delirium.

**Table 1. tab1:** Data collection methods and clinical assessment time points.

contents	Study period							
	T0	T1	T2	T3	T4	T5	T6	T7
ENROLLMENT								
Eligibility screening	X							
Informed consent	X							
Demographic characteristics		X						
Baseline measures		X	X					
Randomization	X							
INTERVENTION								
EA			X					
SEA			X					
ASSESSMENTS								
Incidence of POD				X	X	X	X	
Onset time of POD				X	X	X	X	
Duration of POD				X	X	X	X	
Severity of POD				X	X	X	X	
Subtypes of POD				X	X	X	X	
VAS scale				X	X	X	X	
Incidence of CRBD				X				
Opioid consumption						X	X	
Blood test indexes					X	X	X	
Perioperative anxiety score	X				X	X	X	
Safety outcomes	Throughout the study period until discharge							

T0:1 day of pre-surgery T1: 30 min before anesthesia T2: during operation T3:6h post-operation T4:1d post-operation T5: 2d post-operation T6:3d post-operation T7: hospital discharge

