### Intervention

A licensed acupuncturist with at least 3 years of clinical experience will perform the intervention. The protocol adheres to the Standards for Reporting Controlled Trials in Acupuncture (STRICTA) recommendations (27). Acupuncture will be performed 30 min prior to anesthesia induction. The acupoints Zusanli (ST36) and Baihui (GV20) were selected based on Traditional Chinese Medicine (TCM) theory and prior evidence suggesting their efficacy in regulating inflammatory responses and improving cerebral function, respectively.

Sterile, disposable stainless-steel needles (0.30 mm × 75 mm; Hwato Brand, Suzhou Medical Appliance Factory, China) will be inserted at the bilateral ST36 and GV20. Acupoint localization follows the WHO Standard (28), as detailed in Table 3 and Figure 2. The needles at ST36 will be inserted to a depth of 30–40 mm at a 30–45° angle inward and downward. The needle at GV20 will be inserted to a depth of 10–20 mm at a 15–30° angle posterior and downward. De qi sensation—characterized by soreness, numbness, distension, or heaviness—will be elicited by lifting, thrusting, and twirling the needles. Subsequently, the needles will be connected to an electro-stimulator (HANS-200A, Nanjing Jisheng Medical Co, Ltd) delivering a dilatational wave at 2 Hz. Stimulation will be maintained for 25–30 min. Any acupuncture-related adverse events, such as hematoma, severe pain, dizziness, or needle breakage, will be monitored and recorded.

**Table 3 tab3:** Location of ST36 and GV20.

Location of acupoints for the EA group	
Acupoint	Location
Zusanli (ST 36)	3 cun directly below Dubi (ST35), 1 finger-breadth lateral to the anterior border of the tibia
Bahui (GV 20)	Five cun directly above the midline of the frontal hairline, or at the midpoint of the line connecting the apex of both ears

1 cun (≈20 mm) is defined as the width of the interphalangeal joint of patient’s thumb.

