#### Secondary outcome

1) Number of POD episodes: A positive 3D-CAM assessment will indicate the presence of a POD episode. Transition from POD to non-POD status will be established with two consecutive negative 3D-CAM assessments.2) Onset time and duration of delirium: Onset time of delirium will be defined as the duration from the subject’s return to the surgical ward to the initial delirium diagnosis. Duration of delirium will include the period from the subject’s delirium diagnosis to the occurrence of two negative 3D-CAM assessments. The longest duration of delirium will be recorded for patients experiencing multiple episodes.3) Delirium severity score: Patients with confirmed delirium will undergo assessment for delirium severity utilizing the Confusion Assessment Method-Severity (CAM-S) (32), with daily maximum scores documented. The CAM-S scale comprises four items, yielding a total score of 7 points. Severity grading includes absent (0), mild (1), or marked (2), with a total score of 0 indicating normalcy, 1 signifying mild delirium, 3–5 indicating moderate delirium, and 6–7 representing severe delirium.4) Subtypes of delirium: Delirium subtypes—hyperactive, hypoactive, and mixed—will be determined based on clinical manifestations. RASS will be utilized to classify delirium subtypes, with hyperactive delirium characterized by consistently positive RASS scores (+1 to +4), hypoactive delirium denoted by consistently neutral or negative RASS scores (−3 to 0), and mixed delirium indicated when both positive and neutral/negative RASS scores are observed.5) Pain scores: Postoperative pain at rest will be assessed using the Visual Analog Scale (VAS) during the scheduled afternoon assessment window (16:00–18:00) on postoperative days 1–3.6) Opioid consumption: Opioid consumption, including PCIA and rescue analgesics, will be quantified on postoperative days 1 and 2. Opioid consumption will be converted to a “morphine equivalent dose” for analysis.7) Blood test indexes: Venous blood samples (5 mL) will be collected at three time points: baseline (before acupuncture intervention/anesthesia induction), the end of surgery and postoperative day 1. Plasma levels of S100β and P-tau 217 proteins will be quantified via enzyme-linked immunosorbent assay (ELISA).8) Incidence and severity of catheter-related bladder discomfort (CRBD): CRBD severity will be graded on a scale of 1 to 4, ranging from no discomfort to severe discomfort, with corresponding descriptions provided.9) Perioperative anxiety score: Perioperative anxiety will be measured using the Hospital Anxiety and Depression Scale-Anxiety (HADS-A) subscale (33), assessing the incidence of perioperative anxiety from the day of surgery through 3 days postoperatively. The HADS-A consists of seven items and is a commonly used self-assessment scale for evaluating psychological distress in non-psychiatric patients, demonstrating good sensitivity and specificity. Patients with a HADS-A score of eight or above will be considered to have an anxiety disorder.10) Adverse events: Safety endpoints include general postoperative complications (e.g., cardiac arrhythmias, hypotension, cardiogenic shock) and intervention-related adverse events specific to acupuncture (e.g., subcutaneous hematoma, needle site pain, dizziness/fainting, or needle breakage).

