A comprehensive assessment of efficacy will be conducted by analyzing a series of secondary outcomes. For longitudinal continuous outcomes—such as the HADS-A scores measured at multiple time points—a linear mixed-effects model (LMM) will be used to account for within-subject correlation. For pre-to-post changes in biomarkers (P-tau 217 and S100β), an analysis of covariance (ANCOVA) model will be used, with the baseline value included as a continuous covariate to improve statistical precision. For all other secondary outcomes, continuous variables will be compared using the independent samples t-test or the Mann–Whitney U test; ordinal outcomes (such as CRBD severity) will be analyzed with the Mann–Whitney U test, and binary outcomes will be compared using the *χ*^2^ test or Fisher’s exact test. Safety outcomes, including the incidence of adverse events (e.g., acupuncture-related hematoma, dizziness) and general postoperative complications, will also be compared between the groups using the *χ*^2^ test or Fisher’s exact test. Additionally, to assess the success of blinding, the agreement between participants guessed and actual treatment allocation will be quantified using Cohen’s Kappa coefficient.

Two exploratory analyses will be conducted. First, to identify potential predictors of POD, we will perform separate univariable logistic regression analyses for key intraoperative variables (e.g., duration of anesthesia, estimated blood loss), reporting unadjusted odds ratios and 95% CIs. Second, we will investigate the association between these variables and the treatment effect to generate hypotheses for future research.

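### Blood sampling for P-tau 217 and S100β is specified in three incompatible ways, and only one of them clearly supplies the pre-treatment baseline that the planned ANCOVA needs

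*Protocol article*

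**What the plan says.** All references are to the protocol article.

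- **Secondary outcome, item 7.** Samples "will be collected at three time points: baseline (before acupuncture intervention/anesthesia induction), the end of surgery and postoperative day 1".
- **Additional consent provisions.** Here "a 5 mL venous blood sample will be collected at two time points: immediately before anesthesia induction and at the end of surgery". No draw on postoperative day 1 is mentioned, and the first sample is not called a baseline.
- **Table 1.** The row "Blood test indexes" is marked at T4, T5 and T6, which the key defines as "T4:1d post-operation T5: 2d post-operation T6:3d post-operation". The row has no mark before surgery or at the end of surgery. A separate row, "Baseline measures", is marked at T1 and T2, and its contents are not listed.
- **Intervention.** "Acupuncture will be performed 30 min prior to anesthesia induction", with stimulation for 25–30 min.
- **Statistical analysis.** For pre-to-post changes in the two biomarkers, "an analysis of covariance (ANCOVA) model will be used, with the baseline value included as a continuous covariate".
- **Plans for collection, laboratory evaluation and storage.** Draws are described only as baseline and postoperative, so this section does not settle which schedule applies.

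**The concern.** A condensed article may leave detail out. This one states detail three times, and the statements cannot all be true. The schedule decides which data will exist, and a sample that is missed or drawn at the wrong moment cannot be recovered.

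The ANCOVA needs a value unaffected by treatment. One schedule has no preoperative blood draw in its row. Another places the first draw after the intervention has essentially been delivered. The third joins two moments about 30 min apart with a slash, so site staff could follow either.

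The Discussion names a smaller postoperative rise in these two biomarkers as a trial hypothesis, and this analysis is the one that addresses it. Recruitment runs from March 2025 to July 2026, and assays are batched after all samples are collected. The laboratory results will therefore not expose a sampling problem while it can still be corrected.

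**Working it through.** The plan states no figure for this point, so there is none to reproduce. The check is a comparison of the schedules, a timeline, and the algebra of an ANCOVA with a post-treatment covariate.

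**1. Schedules side by side**

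| Source | Before surgery | End of surgery | Day 1 | Day 2 | Day 3 |
|---|---|---|---|---|---|
| Secondary outcome, item 7 | yes, before acupuncture/induction | yes | yes | no | no |
| Consent provisions | yes, immediately before induction | yes | no | no | no |
| Table 1, blood row | no | no | yes | yes | yes |

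No column is filled in all three rows. The consent section and the Table 1 row share no time point at all.

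**2. Could Table 1 be a reading error?** The delirium rows fall at T3–T6, which matches the primary outcome text (6 h, then days 1–3), so the columns appear to read correctly. Moving the blood row one column either way (T3–T5 or T5–T7) still does not give baseline, end of surgery and day 1.

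**3. Could the generic baseline row hold the missing sample?** Possibly, since its contents are not listed. But the anxiety row carries its own preoperative mark at T0, and the blood row has none. The generic row is also marked at T2, the column in which the intervention is marked, so it is not clearly pre-treatment.

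**4. Timeline, with induction at 0 min.** The intervention starts at −30 min. Stimulation ends between −30 + 25 = −5 min and −30 + 30 = 0 min. A draw immediately before induction therefore falls at or after the end of stimulation.

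**5. Effect on the ANCOVA if that draw is used as baseline.** Let Δ be the total effect on the post-surgery value, β the slope of the post-surgery value on baseline, and δ the shift already present at the draw.

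ANCOVA estimate = Δ − β × δ

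If a share f of the effect is already present (δ = fΔ), the fraction retained is 1 − βf:

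| β (assumed) | f = 0 | f = 0.25 | f = 0.5 | f = 1 |
|---|---|---|---|---|
| 0.3 | 1.00 | 0.925 | 0.85 | 0.70 |
| 0.5 | 1.00 | 0.875 | 0.75 | 0.50 |
| 0.7 | 1.00 | 0.825 | 0.65 | 0.30 |

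A simulation agrees (106 per arm, 3,000 runs, assumed Δ = −0.40 SD, β = 0.5):

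| Share f present at the draw | Baseline before the intervention | First draw after the intervention |
|---|---|---|
| 0 | −0.400 | −0.400 |
| 0.25 | −0.397 | −0.347 |
| 0.5 | −0.397 | −0.297 |
| 1 | −0.401 | −0.201 |

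The documents give no value for Δ, β or f. All three are assumptions.

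**The case against.** The strongest reply is that a valid schedule is already written. The outcome definition places baseline before acupuncture. Acupuncture precedes induction, so a draw before needling satisfies both halves of the slash. On that reading the ANCOVA is feasible and unbiased. This stands. A reader might infer that the analysis is impossible or biased whichever text is followed, and the documents do not support that: the covariate is missing only under the Table 1 blood row, and attenuation can arise only with the draw in the consent section.

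The attenuation is also conditional. The stated hypothesis concerns a rise after surgery, and nothing in the documents shows that these biomarkers move within about 30 min of needling, before any incision. With no early shift there is no bias. Since β is below 1 in the cases considered, adjustment removes part of an early effect and not all of it. For a shift in the same direction as the final effect, the result is understatement and not a spurious benefit. The groups also remain randomised, so post-surgery values could still be compared without the covariate.

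A reader might further infer that day 1 samples are being taken without consent. The article only summarises the consent form, and the form is not shown, so this cannot be established.

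Finally, the choice of the post-surgery time point for the ANCOVA may be left to an analysis plan that is not shown. That is fair, but an analysis plan cannot supply a sample that the schedule does not collect.

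**Conclusion.** The contradiction is established from the text and does not rest on any assumption. The timing of the pre-induction draw relative to stimulation follows from the protocol's own figures.

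The consequence depends on which text the sites follow:

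- **Outcome definition, drawn before needling:** the ANCOVA is valid.
- **Table 1 blood row:** the ANCOVA has no baseline covariate, unless the unspecified baseline row includes blood.
- **Consent section, with its first draw used as baseline:** the estimate loses β × δ. This ranges from nothing to 70% of the total effect for β of 0.3 to 0.7 and f of 0 to 1, all assumed values. The upper end requires the whole effect to be present before surgery.

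This is an internal inconsistency in one of ten listed secondary outcomes. The delirium endpoint, its mixed model and the sample size are untouched. It should be fixed, and soon, because enrolment is under way.

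**What to change.** 1. State one blood-sampling schedule, identically, in Table 1, in item 7 of the secondary outcomes and in the consent section.
2. Define baseline as a draw completed before needle insertion, in place of the wording with the slash, and record the clock time of the draw and of insertion.
3. Make the post-surgery time points used in the ANCOVA match that schedule.
4. Check that the consent form covers every draw in the chosen schedule, and amend the form or the schedule if it does not.
5. For patients already enrolled, establish when the first sample was taken. Flag those drawn after the intervention began and do not use them as the baseline covariate.

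The cost is corrected wording in three places, an ethics amendment if the consent form or the approved schedule has to change, and a review of sampling times to date. If the outcome definition is adopted, no procedure is added beyond what that section already plans. Whether the first draw has to move depends on what the sites now do, which the documents do not say.
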